#### **13.5. Confidentiality**

Participant confidentiality is strictly held in trust by the participating investigators, their staff, and the research team. This confidentiality is to cover the clinical information relating to participants. All data will only be referenced by numerical identifier code. Data will be stored on a password-protected computer. A key connecting names and code numbers will be kept in a locked cabinet, accessible only by research personnel. All data will be stored and analyzed on password-protected computers, also only accessible by research personnel. Participants will not be identified in any report or publication about this study. See 12.2. *Privacy, Security, and Data Confidentiality* for more information on source documentation storage and security.

#### **13.6. Study Discontinuation**

In the event that the study is discontinued, subjects who have completed or who are still enrolled in the study will be notified. Any new information gained during the course of the study that might affect subjects' safety or willingness to continue participation in the study will be communicated to participants by the study coordinator within 2 days after the Principal Investigator learns this information.

### **14. Data Analysis**

#### **14.1. Sample Size Considerations and Study Feasibility**

For this pilot feasibility trial, we aim to recruit 20 participants in total.

## **14.2. Clinical Outcomes Analysis**

We are primarily interested in precise estimates of tolerability, outcome variability, and preliminary effectiveness of FES compared to sham FES in patients with MDD that will aid in the planning of a larger, sufficiently powered efficacy trial.

Initial analyses will summarize socio-demographic and clinical characteristics by treatment group. Primary analyses will be performed on the modified intention-to-treat (ITT) population, including all randomized participants that received at least one FES treatment. The feasibility outcome defined as overall dropout rates will be summarized using descriptive statistics such as counts and percentages. Feasibility analyses will report feasibility outcomes using descriptive statistics with counts and proportions for categorical data and means and standard deviations or median and interquartile range, as appropriate, for continuous data. The proportion lost to follow-up will be estimated along with a 95% confidence interval. The lower 95% confidence limit should be at least 90% to proceed. The proportion compliant with the protocol, including treatment compliance as well as study completion and complete data on clinical outcomes will be estimated with 95% confidence interval. For validity to be fairly high, the lower 95% confidence limit should be >90%. The blinding index proposed is scaled to an interval of -1 to 1, 1 being a complete lack of blinding, 0 being consistent with perfect blinding and -1 indicating opposite guessing, which may be related to unblinding.

The preliminary effectiveness analysis will report the between group difference in change from baseline to treatment 20 in the HAM-D-17 and its 95% confidence interval, using analysis of covariance (ANCOVA), with 20 treatment HAM-D-17 as the outcome and baseline HAM-D-17 and stratification variables (sex) as covariates. We will also report estimates for standard deviation of HAM-D-17 score and within-person correlation between baseline and follow-up HAM-D-17 scores. A similar approach will be used for all other continuous variables for secondary outcome measures (e.g., QIDS-SR, GAD-7, etc). Differences between groups in dichotomous outcomes (e.g., response, remission, adverse effects) will be described using an odds ratio and 95% confidence interval. To explore the sustainability of the treatment effect, we aim to also report changes of HAM-D-17 scores during the month after 20 treatments. The success of blinding of patients will be assessed by computation of Bang's blinding index. Sex and gender stratified analysis will be carried out.

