## **8. Outcome Measures**

### **8.1. Primary Outcome Measures**

The primary outcome will be the feasibility, tolerability, and safety outcomes that include the recruitment, dropout, data completion, and protocol compliance rates, as well as the number and nature of AEs and SAEs. Self-report questionnaires will be completed via REDCap.

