### **9.2. Potential Risks and Analysis of Risk/Benefit Ratio**

#### 3D mask

The materials used for printing the FES mask are chosen to be biocompatible and chemically stable, similar to the conventional polymeric materials used in wearables. Therefore, it is expected

that there will be no skin sensitivity to the mask's material itself. However, we will monitor the user's face after experiencing multiple courses of stimulation. If any skin reaction (e.g., redness and bruising) is observed on the user's face, we will switch to other available biocompatible materials for the mask.

Due to the potential geometrical mismatches between the mask and face, which might originate from either the scanning process or CAD design steps, there is a possibility of the user's discomfort or ineffective contact with the skin when wearing the mask. To address this issue, we will check with the user for any discomfort or geometrical mismatch when they put on the mask and determine the problematic regions. Then, we can adjust the CAD design and modify the geometry of those regions so that we can reprint and deliver a modified mask with the best design based on the functionality and user's experience.

We are using mechanically flexible and durable materials for printing the masks, which we expect to be robust and not damaged easily, e.g., if it accidentally falls down from the face. However, in case of a fracture or any other damages that may occur when using the mask, we would ask the user to stop wearing the mask and inform us about the damage type and shape. For small damages, we might be able to repair the mask by standard adhesion methods, while for large damages, we can simply print a new mask and deliver it to the user, as we already have the final 3D model design, and we can simply run the 3D printing step for a new mask mold and then create a new mask.

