#### **11.2.2. Collection of AEs**

The condition of the participant will be monitored throughout the study. At each visit, whether scheduled or unscheduled, AEs will be elicited using the scale of the adverse events. In addition, the Investigator will check the participant records for any documented event.

All AEs, including local and systemic reactions not meeting the criteria for “serious adverse events”, will be captured on the appropriate CRF. If the participant reports several signs or symptoms representing a single syndrome or diagnosis, the diagnosis should be recorded in the

CRF. In addition, the AE Report Form will be completed by the study coordinator. The AE Report Form includes the following:

- What is known about the therapy
- What is known about previously reported side effects
- If the AE occurred in temporal relation to the therapy
- Whether or not the AE improves or disappears when treatment is stopped
- Whether the AE is worsening of baseline symptoms
- Whether the AE is related to a concurrent medical condition or medication use

Once complete, this form will be given to the Principal Investigator and Co-Investigators, who will review, comment on, and sign this form. The Investigator will grade the severity of all AEs (mild, moderate, or severe), the seriousness (non-serious or serious), and the likelihood that they were related to the FES stimulation (causality). Completed forms will be placed in the participant's folder.

In addition, the study coordinator will document any AE occurrence on the AE log, which includes information such as the date of the AE, severity, relationship to the treatment (assessed by the Principal Investigator and Co-Investigators), actions taken, and outcome(s). The log will be reviewed and initialed by the Principal Investigator 72 hours after being completed. All AEs occurring during the clinical trial will be documented appropriately regardless of the relationship to FES. All AEs will be followed to adequate resolution and will be graded for severity and relationship to study treatment. Any medical condition noted at the initial session will be considered at baseline and not reported as an AE unless an exacerbation in intensity or frequency (worsening) occurs.

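### Dropout, compliance and data completion are estimated only in randomized participants who had at least one FES treatment, so anyone randomized who leaves before session 1 is not counted as a dropout

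*Protocol*

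**What the plan says.** Section 14.2 places the primary analyses on the "modified intention-to-treat (ITT) population, including all randomized participants that received at least one FES treatment". The primary outcomes, in section 8.1 and in the trial summary (section 1), are feasibility, tolerability and safety, comprising "recruitment, dropout, data completion, and protocol compliance rates, as well as the number and nature of AEs and SAEs". Directly after defining the analysis set, section 14.2 turns to attrition: "The feasibility outcome defined as overall dropout rates will be summarized using descriptive statistics such as counts and percentages". It then adds: "The proportion lost to follow-up will be estimated along with a 95% confidence interval". No other analysis set is named for these outcomes.

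On the timing of randomization:
- Table 1 marks allocation and mask delivery together at timepoint -1, ahead of baseline at timepoint 0 and session 1.
- Section 6.1 assigns arms only when the baseline measures of Visit 0 are complete, which is after both mask visits.

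On safety:
- Section 6.3 describes stimulation before session 1, as a pilot test at mask development and a test with the mask at mask delivery.
- Section 11.1.1 collects adverse events from the start of the experimental protocol, and section 11.2.2 elicits them at every visit. The self-report adverse-event row in Table 1 begins at Visit 1.
- Section 11.2.2 also says: "Any medical condition noted at the initial session will be considered at baseline and not reported as an AE unless an exacerbation".

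**The concern.** A modified ITT set that requires one treatment is a usual choice for a preliminary efficacy estimate. It does not suit an estimate of attrition, because someone who is randomized and leaves before being treated is one of the events to be counted. The device is a prototype, and section 9.2 itself foresees "discomfort or ineffective contact with the skin when wearing the mask", so losses between receiving the mask and the first session cannot be assumed to be nil.

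Section 14.2 says that the trial exists to inform a larger, adequately powered trial. A dropout rate that is too low, with compliance and completion rates that are too high, would be carried into that trial's sample size and logistics. The error runs in one direction only.

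**Working it through.** **Inputs.** Target sample size 20 (section 14.1); anticipated dropout 15% (section 5.3); analysis set as in section 14.2. The number lost between randomization and session 1 is not in the protocol, so it is varied over its whole range.

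**The plan's own figure.** Section 5.3 says that 15% dropout was built into the sample size, but section 14.1 gives only the total of 20, with no effect size, SD or precision target. The 20 cannot be reproduced. As a consistency check, 20 × 0.85 = 17, but the protocol never states 17 evaluable participants. The 15% serves below only as the protocol's own expectation: 0.15 × 20 = 3 dropouts.

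**Formula.** Let D be the dropouts among 20 randomized, of whom k leave before session 1.
- All randomized: D/20.
- Modified ITT: (D − k)/(20 − k).
- Difference: D/20 − (D − k)/(20 − k) = k(20 − D)/[20(20 − k)], which is never negative. The modified ITT rate is therefore equal or lower, never higher.

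**D = 3** (all randomized: 3/20 = 15.0%, exact 95% CI 3.2 to 37.9):

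| Lost before session 1 (assumed) | Modified ITT dropout | Exact 95% CI |
|---|---|---|
| 0 | 3/20 = 15.0% | 3.2 to 37.9 |
| 1 | 2/19 = 10.5% | 1.3 to 33.1 |
| 2 | 1/18 = 5.6% | 0.1 to 27.3 |
| 3 | 0/17 = 0.0% | 0.0 to 19.5 |

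Each early loss lowers the estimate by about 4.5 to 5.6 percentage points.

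**D = 5 (assumed).** The all-randomized rate of 25.0% becomes 21.1%, 16.7%, 11.8%, 6.25% or 0% with one to five early losses.

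**Compliance moves the other way.** If 17 of 20 randomized comply (85.0%) and the other three are the dropouts above, the modified ITT figure is 17/19 = 89.5%, 17/18 = 94.4% or 17/17 = 100% with one, two or three early losses.

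**Which losses fall in the window.**

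| Point of loss | Table 1 (allocation at -1) | Section 6.1 (after Visit 0 measures) |
|---|---|---|
| Mask development | before randomization | before randomization |
| After allocation at mask delivery, up to Visit 0 | randomized, excluded by modified ITT | before randomization |
| After randomization at Visit 0, before session 1 | randomized, excluded by modified ITT | randomized, excluded by modified ITT |

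Sections 6.2, 6.3 and 7 lean towards Table 1: the stimulator handed over at mask delivery is already programmed, and the arm's pattern is in the device. Against that, section 6.3 lets baseline assessment take place on the first stimulation day, so under section 6.1 the window could shrink almost to nothing.

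**Check on the 90% limit.** Read as retention, the exact lower 95% limit when nobody is lost is 0.025^(1/n): 83.2% for 20/20 and 80.5% for 17/17. Both are below 90%.

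**The case against.** The strongest reply is that the window may be very short. If section 6.1 governs, people lost at either mask visit were never randomized, and the modified ITT rule is not what removes them. That stands, and it limits the size of the effect. It does not remove the flaw, because the rule still drops anyone lost between randomization and session 1. It also means that an all-randomized set alone would miss mask-stage failures, so these need their own count.

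A second reply is that the protocol does not say that this set is the only one. Recruitment cannot be computed in treated participants, CONSORT reporting (section 15.3) would show those randomized but untreated, and a separate analysis plan may define further sets. This is fair as far as it goes. But the protocol does fix a set for its primary analyses, and that set is wrong for attrition.

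Third, the pilot study described in section 3 reported full adherence, and section 9.2 provides for reprinting an ill-fitting mask. Early losses may therefore be few, which is why the figures above are a range and not a forecast.

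On safety, a treated-only set is conventional, and sections 11.1.1 and 11.2.2 already collect events at the mask visits. A reader might infer from Table 1 that those events go unrecorded, or from section 11.2.2 that a skin reaction to the mask-visit tests would be reclassified as baseline. The documents do not support either inference. The Table 1 row covers one self-report instrument. The initial session is undefined in section 11.2.2, section 13.4 uses the same term for an eligibility step, and worsening would be reported in any case. What remains is an inconsistency to align, together with the point that someone stimulated at a mask visit who never starts session 1 lies outside the modified ITT set.

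**Conclusion.** The point holds for the feasibility rates. The analysis set in section 14.2 can only leave the dropout estimate unchanged or bias it downward. At 15% true dropout in 20 randomized, the understatement is 4.5, 9.4 or 15 percentage points with one, two or three losses before session 1, and nil with none. These counts are assumptions. How many losses are possible depends on whether Table 1 or section 6.1 describes when randomization happens, and the protocol does not settle this.

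A reader might go further and conclude that the choice of set could reverse the decision to proceed. It could not with exact limits: if the 90% criterion is read as retention, it is missed even with no losses at all, under either set. The harm is a biased planning figure for the next trial, not a changed decision. It would also be wrong to say that all mask-fitting failures are randomized participants lost to the analysis, since those at mask development precede randomization on either reading.

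**What to change.** - In section 14.2, estimate dropout, loss to follow-up, compliance and data completion in all randomized participants, counting those who never start session 1 as dropouts.
- Report separately the losses between consent and randomization, including mask failures, with the stage and reason.
- Keep the modified ITT set for the HAM-D-17 and the other effectiveness estimates.
- Reconcile section 6.1 with Table 1, and with the pre-programmed device described in sections 6.2, 6.3 and 7, so that the point of randomization is stated once.
- For safety, count adverse events from first stimulation, including the tests at mask development and mask delivery. Align the Table 1 adverse-event row and the term used for the baseline occasion in section 11.2.2 with section 11.1.1.

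The cost is wording plus the existing adverse-event form at two visits that already take place. The sample size is unchanged. The one downside is that the reported rates may be slightly less favourable.

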### **5.3. Method of Recruitment**

The single study center will be the Interventional Psychiatry Program at St. Michael's Hospital, Unity Health Toronto (SMH, UHT). The subjects will be recruited from the Interventional Psychiatry Program at St. Michael's Hospital, Unity Health Toronto. The target recruitment rate is a total of 20 subjects recruited over 6 months. Considering our prior experience with this type of study, we do not anticipate any significant compliance issues. We note that the 5 sessions per week proposed here exceeds the schedule in the preliminary study by 2 sessions per week with the presence of a sham arm; we have included a conservative 15% dropout rate in our sample size calculations. However, a 5 session per week schedule is well tolerated in rTMS for MDD and in FES for stroke rehabilitation. Notably, since the intervention includes monitored home-based visits, treatment adherence will be known with 100% accuracy.

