**Table 1: Study Schedule**

## 6.2. Randomization and Blinding

Participants will be randomized in a 1:1 allocation to receive FES (active pattern) or FES (sham pattern). Block randomization will be computer-generated, and the samples will be stratified for sex, given the potential differences in response and tolerability in these groups. A biostatistician will generate the randomization schedule, to be administered by a research assistant who is not associated with the study and instructed not to divulge group assignments to the participants to allow for concealment.

Participants and most study staff will be blinded. Only the physical therapist will need to monitor the participant. Measures taken to prevent functional unblinding include sensory and non-patterned sham and delivering automated messages to both active and sham groups. We will also evaluate each participant's ability to discriminate what treatment they received after each session to assess blinding effectiveness.

We will randomize subjects to study arms (20 days active or 20 days sham) using a secure online randomization module on REDCap. The block size will be fixed, and study personnel will be blinded to the randomization block size. An independent assistant, external to the study, will manage the randomization of subjects. The subject number and treatment code will be assigned

after the subject details have been obtained. Based on this information, the independent assistant will assign a unique subject number and treatment code, which will dictate the treatment assignment for the subject. The patterns will be pre-programmed into the take-home device by the biomedical team.

An unblinded code sheet that matches these stimulation codes to the treatment arm will be kept by an external coordinator and will not be available to the study coordinator or research assistants. The unblinded code sheet will have the following information:

1. The initial identifier codes for all potential participants
2. Stimulation code: 6-digit numerical code for the stimulation session
3. Condition number: Numerical code for the condition
4. Condition name: Name of the condition

A copy of this code sheet with the condition name removed will be provided to the study coordinator and research assistants. These linked codes ensure that the study coordinator and research assistants are kept blinded to the type of treatment each participant will receive.

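### The only stated condition for proceeding is attached to the proportion lost to follow-up, so its direction is reversed and zero dropout fails it

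*Protocol*

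**What the plan says.** Dropout is among the primary feasibility outcomes in Protocol section 8.1. For its analysis, section 14.2 states: "The proportion lost to follow-up will be estimated along with a 95% confidence interval". The next sentence is the decision rule: "The lower 95% confidence limit should be at least 90% to proceed". No other quantity comes between the two.

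Section 14.2 then turns to the proportion compliant with the protocol, which includes study completion and complete outcome data. There it says: "For validity to be fairly high, the lower 95% confidence limit should be >90" per cent.

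Three other statements bear on the rule:

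- Size (section 14.1): "For this pilot feasibility trial, we aim to recruit 20 participants in total". No derivation is given.
- Expected dropout (section 5.3): "we have included a conservative 15% dropout rate in our sample size calculations".
- Population for the primary analyses (section 14.2): the modified ITT set, "including all randomized participants that received at least one FES treatment".

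The protocol does not name the interval method. No other section restates or corrects the rule. Section 10.4 lists reasons for terminating the study but gives no numerical retention criterion.

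**The concern.** A lower confidence limit of at least 90% is a sensible demand on a proportion that should be large. Loss to follow-up should be small. Read as written, the rule lets the programme go forward only if the pilot shows that at least nine in ten participants were lost.

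Section 14.2 says the pilot's purpose is to inform the planning of a larger, adequately powered trial, and this is the only sentence in the protocol that sets a numerical condition for going on. If it is applied literally, it blocks a pilot with perfect retention. If it is applied by guessing the intent, the progression criterion is no longer prespecified, and the guess may be made by people who already know the dropout count.

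**Working it through.** **Inputs.** n = 20 (section 14.1); threshold 90% on the lower 95% limit, and quantity = proportion lost (both section 14.2); expected dropout 15% (section 5.3), that is 0.15 × 20 = 3 participants. I take the proportion over both arms together. The protocol gives no calculation behind the 90% or the 20, so there is no figure to reproduce.

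**Step 1: the literal rule.** Let x be the number lost. The exact (Clopper-Pearson) lower limit is 0 when x = 0. When x = n it solves pⁿ = 0.025, so it equals 0.025^(1/n). For n = 20: 0.025^(1/20) = exp(−3.689/20) = 0.832. All 21 outcomes, x = 0 to 20, were checked under five two-sided 95% intervals:

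| Method | Lower limit, 0/20 lost | 3/20 lost | 20/20 lost | Outcomes with lower limit ≥ 90% |
|---|---|---|---|---|
| Clopper-Pearson | 0% | 3.2% | 83.2% | none |
| Wilson | 0% | 5.2% | 83.9% | none |
| Agresti-Coull | 0% | 4.4% | 81.0% | none |
| Jeffreys | 0% | 4.4% | 88.3% | none |
| Wald | 0% | 0% | 100% | 20/20 lost only |

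The Wald entry arises because the estimated standard error, √(p(1−p)/n), is zero at p = 1, so the interval collapses to a point. A one-sided 95% exact limit does not help either: 0.05^(1/20) = 86.1% with all 20 lost. If the modified ITT set is smaller than 20, the highest exact limit, 0.025^(1/n), only falls.

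**Step 2: reverse the direction and keep the 90%.** Let x now be the number retained. The exact lower limits are:

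| Retained | Exact lower 95% limit |
|---|---|
| 20/20 | 83.2% |
| 19/20 | 75.1% |
| 18/20 | 68.3% |
| 17/20 (the expected 15% dropout) | 62.1% |

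None reaches 90%. The same holds for the equivalent statement that the upper limit on loss be at most 10%: with 0/20 lost the exact upper limit is 1 − 0.832 = 16.8%. Wilson, Agresti-Coull and Jeffreys limits also stay below 90% at 20/20 (83.9%, 81.0% and 88.3%).

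**Step 3: how many participants a 90% lower limit needs.** With no losses, 0.025^(1/n) ≥ 0.90 requires n ≥ ln 0.025 / ln 0.90 = 35.01, so n = 36. The corresponding smallest n is 35 for Wilson, 42 for Agresti-Coull and 24 for Jeffreys. With one loss the exact method needs 54.

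**The case against.** The best defence is that this is a slip whose intent is plain. The neighbouring criterion puts a lower limit above 90% on compliance, where it makes sense, and a 15% dropout assumption cannot sit with a demand for 90% loss. No sensible reader would think the sponsor wants participants to leave. The estimate of loss and its interval would be reported unchanged, and no participant's treatment and no effect estimate depends on the sentence. All of that stands. It does not make the rule usable, because the evident intent, retention with a lower limit of 90%, is also out of reach at this sample size for every interval checked except Wald.

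Two stronger readings are tempting and should be resisted:

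- A reader might infer that the reversal is what makes every result fail. It is not. That impossibility comes from pairing a 90% limit with 20 participants, and it also depends on the interval method, which the protocol leaves open. With 36 or more participants and exact limits, the reversed rule could be met by losing everyone. What the reversal does on its own is make good retention count against proceeding.
- A reader might infer that analysts will have to rewrite the rule after seeing the data. Nothing in the protocol forces that, since the sentence can be amended beforehand.

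Nor does a possible SAP answer the point. The protocol states the rule and states it wrongly, so a corrected SAP would contradict it.

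**Conclusion.** The point holds as a rule that is wrong as written, not as missing detail. Zero dropout fails it whatever the interval method. With the planned 20 participants, none of the 21 possible outcomes passes under the four non-degenerate intervals, and the sole formal pass, under Wald, is the loss of every participant.

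These statements assume that the proportion is taken over both arms, that the denominator is 20 or fewer, and that the limit comes from a 95% interval. The claim that no result can pass should be made only with the sample size and interval method attached. The claim about direction needs no such condition.

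**What to change.** Amend section 14.2 before any outcome data are seen:

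1. State the rule on the proportion retained, or as an upper confidence limit on the proportion lost.
2. Keep the modified ITT denominator, or say openly that it is being changed. State the time point too: follow-up visits run to Visit 24, so ending the count at Visit 20 would be a change that needs stating.
3. Name the interval method, for example Clopper-Pearson. Avoid Wald, which collapses when everyone or no one is lost.
4. Reset the statistic or the threshold so that 20 participants can meet it. One choice is a rule on the point estimate with the interval reported alongside. Another is a lower limit no higher than 83.2%, the exact value at full retention. A 90% point estimate would need 18 of 20 retained and would fail at the 3 losses implied by the planned 15%, so the threshold and the dropout assumption should be set together.
5. Check the companion compliance threshold at the same time, because the same arithmetic applies to it.

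The cost is a short amendment and a less demanding stated progression criterion. Keeping a 90% exact lower limit would instead need at least 36 participants with no losses, or 54 with one.

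### With 20 participants, a lower 95% confidence limit above 90% for compliance is out of reach under the standard intervals, even if all 20 comply

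*Protocol*

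**What the plan says.** Protocol section 14.1 gives the sample size in one sentence, without a precision or power calculation: "For this pilot feasibility trial, we aim to recruit 20 participants in total".

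Section 14.2 bases the primary analyses on a modified intention-to-treat population, "including all randomized participants that received at least one FES treatment", and sets two benchmarks at 90%:

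- **Compliance.** "The proportion compliant with the protocol, including treatment compliance as well as study completion and complete data on clinical outcomes will be estimated with 95%" limits. The benchmark follows: "For validity to be fairly high, the lower 95% confidence limit should be >90" per cent.
- **Loss to follow-up.** "The proportion lost to follow-up will be estimated along with a 95% confidence interval". The next sentence requires a lower 95% limit of no less than 90% before proceeding. As written, that limit belongs to the proportion lost, not the proportion retained.

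Section 14.2 names no interval method. Section 8.1 lists dropout, data completion and protocol compliance among the primary outcomes. Section 5.3 states that "we have included a conservative 15% dropout rate in our sample size calculations".

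**The concern.** The sample size and the 90% benchmark are both fixed in this protocol, and they do not fit together. A lower confidence limit depends on the number of participants as well as on the observed proportion. With 20 participants, even a perfect result leaves a lower limit well under 90% by the usual methods. The benchmark therefore cannot separate a feasible intervention from an infeasible one.

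A trial in which everybody complied would still miss its stated standard for a primary feasibility outcome. The investigators would then have to report a shortfall that the design made all but unavoidable, or set the benchmark aside after seeing the data. Either outcome weakens the case for the larger trial that this pilot is meant to inform.

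**Working it through.** **Inputs**

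- Participants: 20 (section 14.1).
- Denominator: modified intention-to-treat, so at most 20 (section 14.2).
- Benchmark: lower 95% limit above 90% (section 14.2).
- Dropout allowance: 15% (section 5.3).
- Interval method and sidedness: not stated. I take a two-sided 95% interval as the base case and try others.

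The plan has no figure of its own to reproduce, because no calculation links the 20 to the 90%.

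**Step 1: the best possible result, 20 of 20.**

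When everyone complies, the exact (Clopper-Pearson) lower limit solves pⁿ = 0.025:

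- Exact: 0.025^(1/20) = 0.8316

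The Wilson limit reduces to n/(n + z²), with z² = 3.8415:

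- Wilson: 20/23.8415 = 0.8389

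**Step 2: other methods and other counts.** Lower 95% limits, in per cent:

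| Method | 20/20 | 19/20 | 17/20 |
|---|---|---|---|
| Exact, two-sided | 83.2 | 75.1 | 62.1 |
| Wilson | 83.9 | 76.4 | 64.0 |
| Agresti-Coull | 81.0 | 74.6 | 63.1 |
| Jeffreys, equal-tailed | 88.3 | 78.9 | 65.1 |
| Mid-P | 86.1 | 77.7 | 64.4 |
| Exact, one-sided 95% | 86.1 | 78.4 | 65.6 |
| Likelihood ratio | 90.8 | 79.8 | 65.6 |
| Jeffreys, one-tailed | 91.0 | 82.0 | 68.6 |
| Arcsine | 95.3 | 81.5 | 66.5 |
| Wald | 100 (degenerate) | 85.5 | 69.4 |

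The first six rows fail even at 20 of 20. The last four pass there, but no row passes at 19 of 20. A Wald interval with continuity correction behaves like the last four (97.5% at 20 of 20, 83.0% at 19 of 20).

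**Step 3: the sample size the benchmark would need.**

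With nobody non-compliant:

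- Exact: 0.025^(1/35) = 0.89998 just fails and 0.025^(1/36) = 0.9026 passes, so 36 of 36.
- Wilson: 34/37.8415 = 0.8985 fails and 35/38.8415 = 0.9011 passes, so 35 of 35.
- Equal-tailed Jeffreys needs 24, and mid-P needs 29.

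With 1, 2 or 3 non-compliant participants, the exact method needs 54, 70 or 85. A smaller analysed population makes matters worse: 17 of 17 gives 0.025^(1/17) = 0.8049.

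**Step 4: the chance of passing under the permissive methods.** These require all 20 to comply, which has probability p²⁰:

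- true rate 95%: 0.95²⁰ = 0.358
- true rate 90%: 0.90²⁰ = 0.122
- true rate 85%: 0.85²⁰ = 0.039

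The true rates are assumptions, chosen to span a plausible range.

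**Step 5: the rule for proceeding.** Read as retention, it meets the limits in Step 2, so 20 of 20 retained gives 83.2% exact. Read literally, as a lower limit on loss, even 20 of 20 lost gives only 83.2%.

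**Step 6: the dropout allowance.** 20 × 0.85 = 17 retained, for which the exact lower limit is 62.1%. Expressed as loss, 3 of 20 has an exact 95% interval of 3.2% to 37.9%.

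**The case against.** **The interval method is open.** A statistical analysis plan may name it, and some methods pass at 20 of 20. A reader might infer from the exact limit that failure is certain. The documents do not support that: under the likelihood-ratio, arcsine, one-tailed Jeffreys or Wald limit, the chance of passing is low but not zero (Step 4). What remains is that such a choice helps only a flawless trial, and that the Wald interval at 20 of 20 has no width at all.

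**The compliance sentence is not a go/no-go rule.** This is correct. It describes how far the results can be trusted, and only the loss-to-follow-up sentence governs proceeding. Calling the compliance benchmark a decision rule would go beyond the text. It remains a stated standard for a primary outcome.

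**The 15% is a cautious allowance, not a forecast.** This is also correct. Section 5.3 calls it conservative and anticipates no significant compliance problem, and section 3 reports full adherence in the earlier open-label study. The allowance therefore does not show that the plan expects 85% retention. Nor can one infer that the 15% was never applied: 17/0.85 = 20, so the target is consistent with 17 evaluable participants inflated for dropout. The gap is that no such calculation is shown.

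**Sessions could be counted instead of participants.** With 400 sessions, 372 delivered gives a naive exact lower limit of 90.04%. But the proportion in section 14.2 includes study completion and complete data, which belong to participants, and the naive limit ignores clustering within participants.

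**Two further inferences should be resisted.** The stated aim, "We are primarily interested in precise estimates of tolerability, outcome variability, and preliminary effectiveness", sets no precision target and does not name compliance, so it is not contradicted by these limits. And section 14.2 does not say that complete data means every scheduled form, so no completeness rate can be derived from the number of forms.

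**Conclusion.** The compliance benchmark in section 14.2 and the sample size in section 14.1 are incompatible under the exact, Wilson, Agresti-Coull, equal-tailed Jeffreys and mid-P intervals. The shortfall at a perfect result is 1.7 percentage points (Jeffreys, 90 − 88.3) to 9.0 (Agresti-Coull, 90 − 81.0), and 6.8 for the exact limit. Under any method tried, one non-compliant participant is enough to miss it.

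The conclusion rests on participants as the unit, a denominator of at most 20 and a 95% level. It does not depend on whether the exact limit is one- or two-sided. For the rule on proceeding, the same conclusion is conditional on reading it as retention. Its stated direction is a separate matter to settle.

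The benchmark also sits badly with the 15% allowance in section 5.3, because the retention that the allowance tolerates yields a lower limit nearly 28 points under the benchmark (90 − 62.1 = 27.9). That is a tension within the plan, not proof that either figure is wrong.

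**What to change.** Before any data are seen:

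1. In section 14.2, replace the lower-limit criteria with two separate thresholds, one for retention and one for compliance. Set each on the observed count or proportion in the stated modified intention-to-treat population, at a level that 20 participants can attain. State what applies if fewer than 20 are analysed.
2. Report the exact 95% interval beside each result and show how the rule behaves. For example, requiring at least 17 of 20 passes with binomial probability 87%, 65%, 41% and 11% at true rates of 90%, 85%, 80% and 70%. The figure 17 is illustrative. The documents do not dictate it, and the 41% at a true rate of 80% should be weighed before adopting it.
3. In section 14.1, state the precision that 20 participants give, for example 3 of 20 lost with an exact interval of 3.2% to 37.9%.
4. Reconcile section 14.1 with section 5.3 by showing the calculation that includes the 15%, or by removing the reference to one.

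Keeping the 90% lower limit would mean a larger trial. For an 80% chance of passing by the exact method, about 70, 100 or 231 participants are needed if the true compliance rate is 98%, 97% or 95% (assumed rates).

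The recommended change is to wording only and needs no extra participants. Its price is a criterion that reads as less stringent and a stated precision that looks less favourable.
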